#### Secondary outcomes

To explore secondary outcomes, effect size changes will be explored across treatment and follow-up for eating disorder and comorbid symptomatology, general functioning, reflective functioning, parental coping, emotion regulation, expressed emotion and therapeutic alliance. All instruments will be completed at all five time points, except for therapeutic alliance which is not assessed at follow-up timepoints**.**

##### Anthropometric assessment

Height will be measured at beginning and end of treatment by trial researchers. Weight is measured weekly in FT-AN as well as on the first and last day of MFT by clinical staff. Weight and height will be used to calculate percentage of median Body Mass Index (%mBMI) adjusting for age and sex.

##### Psychological symptoms

The Eating Disorder Examination Questionnaire for Adolescents (EDE-A) [60] is a validated instrument of eating disorder symptoms with available adolescent norms [60]. The Revised Children’s Anxiety and Depression Scale (RCADS) [61] will be completed by adolescents and parents to assess depression and anxiety symptoms. The RCADS has been used extensively and shown to have good psychometric properties [62].

##### General functioning

Both parents and adolescents rate the adolescent’s general functioning using the Work and Social Adjustment Scale for Youth (WSAS-Y) [63]. This five-item scale assesses five domains of general functioning: school, daily skills, social, hobbies and family. It has been shown to have good internal consistency and test-retest reliability [63].

##### Reflective functioning

The Reflective Function Questionnaire (RFQ) [64] will be included to measure adolescent’s and parents’ own mentalization and reflective function capacity. It has been shown to be a valid measure of mentalizing capacity [64].

##### Emotion regulation

Adolescent and parents’ own emotion regulation capacity will be assessed using the 18-item Difficulties in Emotion Regulation Scale (DERS) [65]. This is a widely used, validated measure of emotion regulation capacity in adolescents and adults [66, 67]. It has been used recently with an adolescent eating disorder population [20].

##### Parental mood and anxiety symptoms

The Hospital Anxiety and Depression Scale (HADS) [68] is a validated and reliable measure of adult anxiety and depression symptoms in the community setting [69]. It has shown good factor structure and internal consistency [70].

##### Expressed emotion

Level of expressed emotion will be measured using three instruments; one adolescent and two parent-focused. Adolescents will complete the Brief Dyadic Scale of Expressed Emotion (BDSEE) [71], which includes three subscales; criticism, emotional overinvolvement and warmth. The BDSEE has been shown to have good reliability and validity in adolescent and eating disorder populations [71, 72]. Parent’s own perceived level of criticism and overinvolvement will be assessed using the self-report Family Questionnaire (FQ) [73], a valid measure of expressed emotion [73] Parents also complete the verbal Five Minute Speech Sample (FMSS) [74] task. This requires each parent/carer to talk about their thoughts and feelings about the patient for five uninterrupted minutes. This speech is recorded and later coded for overall level of expressed emotion. This is considered a valid measure of expressed emotion [75]. The FMSS will be used to identify EE categories (high/low criticism, high/low emotional overinvolvement, positive/negative relationship). Level of criticism and emotional overinvolvement (continuous variables) will be derived from the BDSEE and FQ for young people and parents, respectively.

##### Therapeutic Alliance

The System for Observing Family Therapy Alliances (SOFTA) [76] will be used to measure therapeutic alliance with the young person as well as parents. The SOFTA includes both a 16-item self-report instrument (SOFTA-s) and an observational tool (SOFTA-o) to analyse both audio and video recordings [77]. Both have been approved for use in this study. The self-report instrument will be used primarily and the observational tool only if data are missing. The SOFTA is widely used and validated for use in family therapy [76]. Baseline SOFTA assessment is completed at two-weeks post randomization, not initial assessment, given therapeutic alliance requires some time in treatment to develop. It is not completed at either six- or 12-month timepoints.

### Data collection, management and confidentiality

All participants will be assigned a unique trial identification number used for randomisation, data collection and analyses. All anonymised data will be stored securely and separately to consent forms in password-protected computers only accessible to the research team. If participants discontinue, weight and treatment characteristics will continue to be collected if consent is provided. Participants are provided with a small financial incentive (£10 voucher) if they complete measures at all five assessment time points.

### Analysis plan

Primary outcomes (feasibility and acceptability) will be reported using means, standard deviations and ranges, or medians and interquartile ranges of the primary outcomes listed above (see Table 1). Numeric feasibility and acceptability parameters (recruitment rate, missing data, loss to follow-up, treatment dropout) will be categorised as either green (> 75% response rate), amber (50–75% response rate), or red (< 50% response rate). Numeric values will also be considered in the context of non-numeric/free-response data where available. Parameters in the red and amber zone will be carefully considered and/or amended for the design of the main trial.

Linear mixed models [78] will be used to explore any changes in secondary outcomes (young person and parent factors) over the treatment and follow-up period. These models are commonly used statistical methods to analyse longitudinal data [79]. Simulation studies have shown them to be robust with moderate sample sizes, as in this study, when the data are normally distributed or lightly skewed [80–82]. This approach allows for random factors (both between and within-subject variability) to be included, meaning individual differences at baseline (e.g., demographic and illness characteristics) can be taken into account, as well as the possibility of individual differences in change trajectories during treatment.

Change in weight will also be calculated for the subgroup who are underweight at baseline (< 90%mBMI) or for whom weight gain is an identified treatment target. Baseline characteristics (gender, illness severity and duration, prior treatment, intact family status) and post-treatment characteristics (additional treatment type and dose, re-referral to services, referral to higher levels of care) will also be reported and groups compared using exploratory t-tests. Group differences between those with available data and those with missing data will also be reported and compared using exploratory t-tests. Together, this will be used to identify variables to be considered as strata for randomisation in the larger trial.

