### Recruitment

The study aims to recruit 60 young people and their families (30 per arm). This is based on guidance from the National Institute for Health Research that a sample size required for a fRCT ranges from 24 to 50 participants [51–54] and other guidance that a sample size as large as 70 may be required [55]. The recruitment site is a research active service. To achieve adequate enrolment in the trial a member of the research team will regularly attend team meetings to answer any questions about the study and identify potential participants.

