#### Primary outcome

Feasibility and acceptability will be assessed using five domains. See Table 1 for each domain and how they will be reported on.

**Table 1 Tab1:** Feasibility and acceptability domains and outcome reporting

*Domain*	*Metric*
Recruitment rate	- Percentage of eligible participants who consent to participate in the study during the study period (18 months)
Feasibility of measurement tools	- The mean time taken to complete questionnaires in minutes. - Amount of missing data per questionnaires reported as a percentage per measure - The number of participants who complete questionnaires at two months, end of treatment (six months), six-month follow-up and 12-month follow-up reported as a percentage of the total sample
Prospective acceptability	- Free text responses for why individuals did not take part or discontinued the trial - Mean responses to the Expectation of Improvement and Suitability of Treatment (EIST). The EIST is a two-item measure assessing how successful and how suitable the participant thinks treatment is.
Acceptability of intervention for participants	- The total number of sessions attended recorded at the end of treatment (six months) - The total number of sessions cancelled with reason recorded at the end of treatment (six months) - The total number of sessions participants did not attend without provided notice recorded at the end of treatment (six months)
Participant satisfaction	- Interview responses during qualitative interviews at the end of treatment (six months).

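### One favourable-rate traffic-light scale grades three adverse rates, uses point estimates only, and takes questionnaire completion on the pooled sample, so a green grade may not separate from amber or speak for the MFT arm

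*Protocol article*

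**What the plan says.** The Analysis plan of the protocol article deals with the primary outcomes in two steps. First, they "will be reported using means, standard deviations and ranges, or medians and interquartile ranges of the primary outcomes listed above (see Table 1". Second, a subset is graded: "Numeric feasibility and acceptability parameters (recruitment rate, missing data, loss to follow-up, treatment dropout) will be categorised" as "green (> 75% response rate), amber (50–75% response rate), or red (< 50% response rate". Numeric values are also to be read alongside free-text data. Parameters that fall in amber or red are to be considered and possibly amended for the main trial. No consequence is stated for green.

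Table 1 (Primary outcome) gives the metrics behind the grades:

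- Recruitment is the "Percentage of eligible participants who consent to participate in the study during the study period (18 months".
- Missing data is a percentage missing for each measure.
- Questionnaire completion at each later time point is "reported as a percentage of the total sample".
- For attendance, Table 1 lists numbers of sessions attended, cancelled and missed. It gives no percentage of participants who drop out of treatment.

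On size, the Recruitment section says: "The study aims to recruit 60 young people and their families (30 per arm". The number comes from published guidance, including that "a sample size required for a fRCT ranges from 24 to 50 participants", and not from the precision needed around the 75% and 50% cut-points.

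**The concern.** The colours are the numerical part of the answer to the primary objective, which is whether adding a five-day MFT week is feasible and acceptable. Three features of the rule weaken that answer.

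1. **Direction.** The bands are worded for a rate where high is good. Missing data, loss to follow-up and treatment dropout are rates where low is good. The article does not say that they are to be inverted, and for dropout it does not say what proportion is graded.
2. **Precision.** The colour follows from the observed percentage alone. With 60 families, or about 30 who are offered MFT, results close to a cut-point could easily fall in the next band.
3. **Pooling.** The objective concerns the addition of MFT, which only the experimental arm receives. A completion percentage on the whole sample can hide a weaker result in that arm.

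What is at stake is a parameter graded green that should have been looked at again before the larger trial. Amber and red trigger that second look; green does not.

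**Working it through.** **Inputs.** N = 60, 30 per arm (Recruitment). Cut-points: green above 75%, amber 50% to 75%, red below 50% (Analysis plan). Completion denominator: total sample (Table 1). The plan gives no calculated figure to reproduce; 2 × 30 = 60 is consistent.

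**Step 1: direction.** Apply the bands as written to an adverse rate r, then to its complement 1 − r.

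| Dropout, loss or missing | As written | As complement |
|---|---|---|
| 10% | red | green |
| 30% | red | amber |
| 60% | amber | red |
| 80% | green | red |

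The two readings disagree in every row. Only the recruitment rate fits the label without conversion.

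**Step 2: lowest green count.** Green needs more than 0.75 × 60 = 45, so 46/60. In one arm it needs more than 0.75 × 30 = 22.5, so 23/30. Both are 76.7%.

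**Step 3: Wilson 95% interval.** Centre = (p + z²/2n)/(1 + z²/n). Half-width = z√(p(1 − p)/n + z²/4n²)/(1 + z²/n). Here z = 1.96 and z² = 3.8415.

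- 46/60: centre = (0.7667 + 0.0320)/1.0640 = 0.7506; half-width = 1.96 × √(0.002981 + 0.000267)/1.0640 = 0.1050. Interval 64.6% to 85.6%.
- 23/30: centre = (0.7667 + 0.0640)/1.1280 = 0.7364; half-width = 1.96 × √(0.005963 + 0.001067)/1.1280 = 0.1457. Interval 59.1% to 88.2%.

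Both intervals cover amber and green; neither reaches red. The lower limit passes 75% only from 52/60 (86.7%) or 28/30 (93.3%). Clopper-Pearson limits give the same two counts.

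**Step 4: chance that the point estimate lands in the wrong band.** Exact binomial, for example P(X ≥ 46 | 60, 0.70) and P(X ≥ 23 | 30, 0.70).

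| True rate (band) | Graded as | n = 60 | n = 30 |
|---|---|---|---|
| 70% (amber) | green | 0.162 | 0.281 |
| 80% (green) | amber | 0.207 | 0.239 |
| 45% (red) | amber | 0.258 | 0.355 |

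**Step 5: recruitment.** Its denominator is the number eligible, which the article does not give. Assuming that 60 consent, 60/79 = 76.0% is green (65.5% to 84.0%) and 60/81 = 74.1% is amber (63.6% to 82.4%). Two more eligible families change the colour while the intervals barely move.

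**Step 6: pooling.** Assumed completion: MFT 18/30 = 60% (amber), control 28/30 = 93% (green). Pooled: (18 + 28)/(30 + 30) = 46/60 = 76.7%, green.

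**The case against.** The best defence has five parts.

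- **The numbers are reported, not just the colours.** This stands. Table 1 requires percentages for recruitment, missing data and completion, and the Analysis plan says that numeric values are weighed with free-text responses. A reader might infer that only the colour will be published; the article does not support that.
- **The summary statistics are not wrong as such.** This stands too. A reader might infer that proportions will be summarised by means and standard deviations. The sentence covers all of Table 1, which includes completion time, expectation scores and session counts, and those summaries suit such items. The wording just does not mention percentages.
- **The grades are advisory.** There is no stop/go rule, and the Discussion calls all conclusions tentative because of the small sample. This lowers the harm. It does not tell a reader how far a particular green is from amber.
- **Intervals and by-arm tables can be left to an analysis plan.** Partly accepted: the article does not forbid either, and their absence alone would be no finding. But the article itself fixes the bands and applies them to the observed percentage, and it is that rule which is weak. A total-sample denominator is also a sensible guard against counting only those who stay. The 18/30 and 28/30 split is an illustration; nothing in the article predicts it.
- **Nobody would call 80% dropout green.** True, and the intended direction can be guessed. The missing definition of dropout cannot be.

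The n = 60 and n = 30 calculations also do not fit every parameter. Recruitment has its own denominator, and several questionnaires are completed by both adolescents and parents.

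**Conclusion.** The concern holds as a weakness of the grading and reporting rule. The label does not fit three of the four graded parameters, and treatment dropout has no defined percentage. A green at the lowest qualifying count is compatible with amber: 65% to 86% for 46/60 and 59% to 88% for 23/30. A true 70% would be graded green with probability 16% at n = 60 and 28% at n = 30. An amber completion rate in the MFT arm can pool to green.

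These figures assume full recruitment, one outcome per family and independent families. MFT is delivered in groups of two to eight families, so any tendency for families in a group to drop out together would widen the intervals for that arm.

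A reader might go further and conclude that 60 is too few or that the cut-points are wrong. The article does not support that: it claims no precision or power for the feasibility outcomes, and nothing here invalidates the sample size or the 75% and 50% limits. The change is worth making, but the trial does not depend on it.

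**What to change.** Amend the Analysis plan and Table 1 as follows.

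1. Word every graded parameter in the favourable direction with its own denominator: consented/eligible; data complete/data due, for each measure; assessed/randomised, at each time point; completed treatment/randomised.
2. Define treatment dropout as a proportion of participants, stating what counts as dropping out, and grade its complement.
3. Report each graded parameter as n/N with a percentage and a Wilson 95% confidence interval. Do so overall and, for parameters measured after randomisation, by arm. Recruitment precedes randomisation and is reported overall only.
4. Keep the colour from the point estimate, and state beside it which bands the interval covers.
5. Add percentages to the sentence on summary statistics, and keep means and medians for the continuous items and counts.

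Leave the 75% and 50% cut-points and N = 60 unchanged. The cost is wording and a few table columns. Trial status says that recruitment is suspended and has yet to commence, so as of this article the change can be made before any data exist. The downside is that some parameters will be shown as compatible with two bands. The fix does not make misgrading rarer; it makes the uncertainty visible.

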### Design

A single-site feasibility randomised controlled trial (fRCT) design will be used. The control group will receive six months of FT-AN. The experimental group will receive six months of FT-AN plus a five-day intensive MFT delivered within the first two months of treatment. See Fig. 1 for participant flowchart. The Standard Protocol Items: Recommendations for Interventional Trials (SPIRIT) checklist [50] was used in the design of this study. See supplementary material for completed checklist.

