#### Five-day intensive multi-family therapy (MFT)

The brief, five-day intensive version of MFT used in this fRCT is an adaptation of the manualised 10-day treatment [32]. During MFT, up to eight families working together with a clinical team over the course of a week to build skills, promote engagement and increase understanding around the illness and family dynamics. The brief intensive version also includes between two and eight families per group and condenses the main treatment content into five full consecutive days (10 am-4 pm) over one week (Monday to Friday). It is delivered by two clinicians. Treatment content matches the phases of FT-AN and focuses on empowering parents to support their child to manage eating disorder symptoms and restore weight. See supplementary material for treatment details, including an example timetable of the five-days.

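### The random structure described for the mixed models names no MFT-group or family level, so the uncertainty of between-arm effects is understated if outcomes correlate within groups or families

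*Protocol article*

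**What the plan says.** **Model.** The Analysis plan section assigns linear mixed models to the secondary outcomes of young people and parents across treatment and follow-up. On the random part it says: "This approach allows for random factors (both between and within-subject variability) to be included". It goes on to say that this accommodates differences between individuals at baseline and in their course over time. Every level it mentions is the individual.

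**Delivery.** The Design section places the group treatment in one arm: "The experimental group will receive six months of FT-AN plus a five-day intensive MFT delivered within the first two months of treatment". The section on five-day MFT gives the group size: "The brief intensive version also includes between two and eight families per group". Each group is run by two clinicians over five consecutive full days. Control families have no such grouping.

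**Parents.** For the speech sample, the Expressed emotion section says: "This requires each parent/carer to talk about their thoughts and feelings about the patient for five uninterrupted minutes". The sections on reflective functioning, emotion regulation, expressed emotion and therapeutic alliance also refer to parents in the plural. The article does not say whether two parents enter a model as two rows, as an average, in separate models, or nested in a family.

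**Purpose.** The secondary objectives are exploratory, carry no hypotheses, and are meant to supply effect sizes for a later full-size trial. Nowhere does the article mention an ICC or a design effect.

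**The concern.** This is a partially nested design. Families in one arm spend a week together with the same clinicians; families in the other arm do not. The Background section attributes the expected added benefit of MFT to features of the multi-family setting itself, such as solidarity and less isolation. If those processes work, outcomes within a group may well be correlated, and a group ICC of zero is not a safe default. Two parents describing the same child are likely to be correlated as well.

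A model with subject-level terms alone treats the 30 experimental families as 30 independent units and, if each parent is a row, treats two parents as two independent units. With positive ICCs, the effect sizes carried forward to the full-size trial would then look more precise than they are. The group-level variance, which a group-delivered main trial has to allow for, would also go unreported.

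**Working it through.** **Inputs from the article.** 60 families, 30 per arm (Recruitment). Groups of m = 2 to 8 families, experimental arm only (Design; five-day MFT section). An 18-month study period (Table 1) and MFT within two months of starting treatment (Design).

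**The plan's own figure.** The sample size of 60 is 30 + 30 and rests on published ranges for feasibility trials (24 to 50, or as many as 70). There is no power or precision calculation to reproduce.

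**Assumptions.** Group ICC 0.02 to 0.10; family ICC 0.2 to 0.5; two parents per family. If recruitment is even and a group starts every two months, there are 18/2 = 9 groups averaging 30/9 = 3.3 families. The extremes are 30/2 = 15 groups of two and 30/8 = 3.75, or about 4, groups near eight.

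**Effect of MFT grouping, one value per family.**
- Design effect in the MFT arm: DE = 1 + (m − 1) × ICC. In the control arm it is 1.
- Ratio of the correct to the unadjusted SE of the arm difference: r = √((DE + 1)/2).
- Actual type I error of a nominal 5% test: 2 × (1 − Φ(1.96/r)).
- Unadjusted 95% half-width: 1.96 × √(2/30) = 0.506 SD. The correct half-width is 0.506 × r.

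| m | ICC | DE | r | Type I error | Half-width (SD) |
|---|---|---|---|---|---|
| 2 | 0.02 | 1.02 | 1.005 | 5.1% | 0.509 |
| 2 | 0.10 | 1.10 | 1.025 | 5.6% | 0.519 |
| 3.3 | 0.02 | 1.05 | 1.012 | 5.3% | 0.512 |
| 3.3 | 0.10 | 1.23 | 1.057 | 6.4% | 0.535 |
| 8 | 0.02 | 1.14 | 1.034 | 5.8% | 0.523 |
| 8 | 0.10 | 1.70 | 1.162 | 9.2% | 0.588 |

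At ICC = 0, r = 1 and nothing is understated.

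A simulation of 20,000 trials per setting (unadjusted comparison at one timepoint) agrees. At ICC 0.10 the type I error is 5.6% with 15 groups of two, 6.3% with nine groups of three or four, and 9.25% with four groups of seven or eight. At ICC 0 it is about 5.1% in each.

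**Effect of pairing parents as independent rows.** Here DE = 1 + family ICC in both arms, r = √DE, and coverage is 2Φ(1.96/r) − 1.
- ICC 0.2: r = 1.095, coverage 92.6%.
- ICC 0.3: r = 1.140, coverage 91.4%.
- ICC 0.5: r = 1.225, coverage 89.0%.

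The simulated type I error is 7.5%, 8.6% and 11.0% respectively.

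**Both together.** With group ICC g and family ICC f, DE is 1 + f + (2m − 2)g in the MFT arm and 1 + f in the control arm. With g = 0.05 and f = 0.3, the MFT-arm DE is 1.40, 1.53 and 2.00 for m = 2, 3.3 and 8, against 1.30 in controls. This gives r = 1.16, 1.19 and 1.28.

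**The case against.** The best defence is that the sentence explains what mixed models can accommodate and is not a full specification. This is a condensed article, and a fuller random-effects structure may stand in a document not shown. A reader might infer that the plan admits subject-level terms and nothing else; the article does not say that. What remains is that the article does describe a random structure and its purpose, and that the structure does not match the delivery it describes elsewhere.

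A reader might also infer that intervals will be too narrow in any event. That is not supported: it needs positive ICCs, and none is given. The article also promises no test or interval from these models, and calls its conclusions tentative. For groups of two or three families the effect is small. The 9.2% figure needs both the largest groups and the largest assumed ICC, and an even recruitment pace points to groups nearer three.

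Nor does the article say that parents are counted as independent subjects. The passage that requires a contribution from each parent concerns data collection, and the speech sample is to be coded into categories, so it is not an obvious outcome for a linear mixed model. The family part of the point is conditional for that reason.

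It would likewise go too far to say that the main trial's sample size will be understated by some percentage. That supposes its designers would ignore clustering, which nothing here says. And with so few groups, this trial can give only a rough group ICC.

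**Conclusion.** The point holds in conditional form. As described, the random structure omits two levels that the design creates: the MFT group in one arm, and the family for parent outcomes. If the models are fitted that way and the ICCs are positive, the uncertainty of between-arm effect sizes is understated. From grouping alone this is modest at the group sizes the timetable suggests (1% to 6% on the SE) and becomes material near eight families per group (up to 16%). For parent outcomes the loss could be larger, but only if both parents enter as independent rows.

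All ICCs are assumed, and the formulas describe a single-timepoint comparison with equal arms. The feasibility and acceptability outcomes and their green, amber and red bands do not come from these models and are not affected. The harm is confined to the precision of exploratory effect sizes intended to inform the full-size trial. It is worth correcting because the correction is cheap.

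**What to change.** 1. Record an MFT group identifier for every experimental family.
2. Specify a partially nested model: a random MFT-group effect in the experimental arm only, with control families as singletons, and small-sample degrees of freedom.
3. For parent outcomes, add a family-level random effect, or use one carer per family named in advance. State which.
4. Report the group and family ICCs with intervals. Because about 4 to 15 groups estimate the group variance poorly, and the estimate may fall at zero, add a sensitivity analysis over assumed group ICCs of 0.02 to 0.10.

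The cost is a few lines of text and one extra data field. Intervals become slightly wider, and the group ICC will be imprecise. Treatment, recruitment and the primary outcomes do not change.

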#### Concomitant treatments and post-trial care

Concomitant psychological treatments are not permitted during this trial. Psychopharmacological treatment is permitted. Medication type, dose and duration will be recorded and reported on. Additional, adjunctive treatments will be available within the same specialist service if any participant should require additional treatment at the end of the six-month treatment trial period. Data on type, duration and intensity of additional treatments will be collected and reported on as part of follow-up data.

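### The t-test is the only test named for a list that includes unordered categories; for an item with three or more of them, the p-value depends on how the categories are numbered.

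*Protocol article*

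**What the plan says.** The third paragraph of the Analysis plan sets out two groups of characteristics and names one test for both. The first group is "Baseline characteristics (gender, illness severity and duration, prior treatment, intact family status"); the second, post-treatment, closes the sentence with the test: "additional treatment type and dose, re-referral to services, referral to higher levels of care) will also be reported and groups compared using exploratory t-tests".

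The same test is then named for a second purpose: "Group differences between those with available data and those with missing data will also be reported and compared using exploratory t-tests". The paragraph also gives the results a use: "Together, this will be used to identify variables to be considered as strata for randomisation in the larger trial".

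On how additional treatment is recorded, the section on concomitant treatments and post-trial care says: "Data on type, duration and intensity of additional treatments will be collected and reported on as part of follow-up data". Type is thus kept apart from amount. The number of categories and their coding are not given.

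No chi-square, Fisher or other categorical test is named in the article. The linear mixed models in the same section are for the secondary outcomes, not for this list.

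**The concern.** The list mixes kinds of variable. Dose, illness duration and severity scores are quantities, and a t-test is reasonable for them. Re-referral, referral to higher care and intact family status may be yes/no. Additional treatment type is nominal, and prior treatment is too if it is recorded by type.

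If a nominal item with three or more categories is held as one variable, the t-test compares the average code number in the two groups. The codes are arbitrary, so the average has no meaning, and two analysts who number the categories differently can get different p-values from the same data. A difference in treatment type could then be flagged or missed because of the numbering.

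The results also feed the choice of candidate strata for the larger trial. That consequence reaches only baseline items, here prior treatment if recorded by type. Additional treatment type arises after randomisation and cannot be a stratum.

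This is not a complaint about a missing detail. The article states a test, and for at least one item it names, that test does not fit unless the item is coded in a particular way.

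**Working it through.** **Inputs.** 30 participants per arm (Recruitment section). The t-test as the only named test (Analysis plan). The article gives no category counts, significance level or sidedness for these comparisons, so there is no figure of the plan's own to reproduce. All counts below are assumed, and two-sided 5% is used for illustration only.

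**1. Three categories, one variable: 18/9/3 v 21/2/7.** With equal arms the pooled statistic is t = (mean₁ − mean₂) / √[(s₁² + s₂²)/30] on 58 degrees of freedom.

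| Codes for the three categories | Means | Variances | t (absolute) | p |
|---|---|---|---|---|
| 1, 2, 3 | 1.500 v 1.533 | 0.466, 0.740 | 0.033/0.200 = 0.17 | 0.87 |
| 1, 3, 2 | 1.700 v 1.367 | 0.838, 0.378 | 0.333/0.201 = 1.66 | 0.10 |
| 2, 1, 3 | 1.800 v 2.167 | 0.372, 0.282 | 0.367/0.148 = 2.48 | 0.016 |

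The other three numberings are reversals of these and give the same p-values.

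Pearson chi-square uses expected counts of 19.5, 5.5 and 5 in each arm: 2(1.5²/19.5) + 2(3.5²/5.5) + 2(2²/5) = 0.23 + 4.45 + 1.60 = 6.29 on 2 df, p = 0.043 under any numbering. The exact Fisher-Freeman-Halton p-value is also 0.043.

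If these proportions were the true ones, power at 5% (40,000 simulated trials) would run from 5% to 70% for the t-test by coding, against 63% for chi-square.

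**2. Four categories, one variable: 18/6/4/2 v 18/2/4/6.** Over all 24 numberings the t-test p-value runs from 0.07 to 0.65. Chi-square is 4.0 on 3 df, p = 0.26; Fisher-Freeman-Halton also gives 0.26. Power is 7% to 45% for the t-test by coding and 34% for chi-square.

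**3. A second three-category table: 15/5/10 v 10/15/5.** The t-test p-value is 0.010, 0.025 or 1.00 by numbering; chi-square gives 0.022. The size of the swing varies with the table, but the dependence on numbering is there each time.

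**4. The same kind of item split into received/not received.** Code dependence disappears.
- 9 v 2 of 30: t = 0.233 / √[(0.217 + 0.064)/30] = 2.41, p = 0.019; chi-square 5.45, p = 0.020.
- 6 v 2 of 30: t-test p = 0.133; chi-square p = 0.129.

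**5. Yes/no items.** Full enumeration of outcomes at 30 v 30 gives a t-test type I error of 5.4%, 4.9%, 4.9% and 5.2% at true rates of 10%, 20%, 30% and 50%. Pearson chi-square gives identical values. No error inflation is claimed for these items.

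**The case against.** The strongest reply is that the fault is conditional. It arises only if an item is held as a single variable with three or more unordered categories and the codes themselves are t-tested. The article says neither. It speaks of treatments in the plural ("Additional, adjunctive treatments will be available within the same specialist service if any participant should require additional treatment"), so one participant may receive several types and separate indicators would be a natural coding, under which the problem goes away (step 4). Prior treatment is affected only if recorded by type. The rest of the list is either quantitative or, as yes/no items, gives nearly the chi-square answer.

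The illustrations also rest on assumed counts. In the four-category table no numbering brings p below 5%, so no conclusion at that level changes. The plan sets no significance level, labels the tests exploratory, treats its conclusions as tentative, and only considers variables as strata. Between randomised arms, baseline differences are due to chance whichever test is used.

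These points stand, and they limit the weight of the concern. They do not remove it. The article names the t-test for the whole list and gives no coding that would make it suitable for treatment type. An exploratory label excuses low power and multiple testing; it does not give meaning to an average of category codes. If the authors intend indicators or a categorical test, the text should say so. The article's brevity is no answer either, because the test it does state is the one that does not fit.

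**Conclusion.** The concern holds in its conditional form. For any listed item held as one variable with three or more unordered categories, the named test gives a p-value that depends on the numbering. Additional treatment type is the clearest candidate, and prior treatment is another if recorded by type. Under assumed counts at 30 per arm the swing can be large (0.016 to 0.87 in one three-category table) or can leave every p-value above 5% (0.07 to 0.65 in the four-category table).

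The conclusion rests on the coding, which is not stated; the dependence on numbering itself follows from the method and not from the assumed counts. Continuous items, yes/no items and items split into indicators are not affected in any way that matters at 30 v 30. The available-versus-missing comparison has the same fault for the same items; its group sizes are unknown, so the 30 v 30 figures do not describe it. The primary feasibility and acceptability outcomes are untouched. This is a minor correction.

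**What to change.** In the third paragraph of the Analysis plan:

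- Limit t-tests to continuous items (dose, illness duration, severity scores).
- For categorical items, report n/N per category by group, with chi-square or an exact test if a p-value is wanted.
- For yes/no items, add a risk difference with a 95% CI. For an assumed 9/30 v 2/30 the difference is 30.0% − 6.7% = 23 points. The Wilson limits are 0.167 to 0.479 and 0.018 to 0.213, which give a Newcombe interval of 0.035 to 0.418, about 4 to 42 points.
- If participants can receive several treatment types, report each type as received/not received.
- Apply the same rule to the available-versus-missing comparison.

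The cost is one sentence and no new data. One small downside is that exact p-values can be larger: for 9 v 2 of 30, Fisher gives 0.042 where the t-test gives 0.019.
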